##### Session 2: intervention (baseline)

Ten days after session 1 (allowing 2 days for synthesis of accelerometry and work-task data), a second session will be held at which the motivational component of the intervention and SSW will be administered. Participants will be provided with feedback on their sitting time and their tasks over the preceding week. They will be asked which of the following three statements, derived from the COM-B questionnaire [37], is most applicable to them: “I do not feel capable of reducing my sitting at work” (capability); “I do not feel I have the opportunity to reduce my sitting at work” (opportunity); “I do not feel motivated to reduce my sitting at work” (motivation). They will then be offered a selection of behaviour change techniques, tailored to their responses to the questions. This portion of the intervention session will be conducted in a private meeting room, and while participants will be free to ask questions at any point, we expect it to take a maximum of 40 min. Participants will also fit themselves with the accelerometer, for data collection purposes only, for a further 7-day wear period.

Following this, a height-adjustable desk-mounted SSW unit will be fitted to their office desk, and they will be provided with ergonomic instructions and accompanying tips. This portion will take a maximum of 20 min.

##### Sessions 3–5: follow ups 1–3 (1, 6, 12 weeks post-baseline)

Participants will be visited on three further occasions (as close to 1, 6 and 12 weeks post-baseline as possible). At each visit, the researcher will collect the accelerometer (fitted 1 week prior by the researcher) and conduct a semi-structured interview. At the final session (12 weeks post-baseline), the SSW will be removed.

#### Intervention content

Our intervention prototype comprises three, sequentially administered components: (a) an initial phase of monitoring and feedback on existing sitting patterns; (b) a ‘menu’ of behaviour change techniques from which participants select techniques tailored to their needs; and (c) provision of a height-adjustable desk for a 12-week period. Intervention content is described more fully, using terminology from the BCT Taxonomy v1 [59], in Additional file 1.

##### Monitoring and feedback

The researcher will provide verbal and visual feedback on participants’ objectively recorded average daily sitting time over the monitoring week (i.e. between sessions 1 and 2), with comparison to their subjective estimate of their sitting time. They will be shown a bar graph, created in Microsoft Excel, of raw data extracted from the accelerometer depicting the average proportion of each hour of the working day (0900 am–1700 pm) spent sitting, standing and walking. This will identify and stimulate discussion of prolonged periods of sitting. The researcher will discuss the task record for the previous week, as well as activity levels during their commute, lunch time and any breaks throughout their working day. The researcher will also provide personalised feedback on the tasks and times of day apparently most conducive to sitting, standing or light activity. Participants will be told of recent research that has linked prolonged periods of sitting and increased risks of heart disease and diabetes [5–8], and will be provided with a set of expert-consensus guidelines for reducing sitting [14]. The aim of this component is to raise awareness of true sitting time and its health implications, and highlight personally relevant work tasks that incur sitting versus those associated with more movement.

##### Menu of behaviour change techniques

Next, participants will receive access to a set of potential behaviour change techniques tailored to their self-declared COM-B barriers to sitting-reduction. Responses to COM-B questions will determine which techniques will be focused upon. After selecting barrier-matched techniques, participants will be offered the option of viewing non-barrier-matched techniques.

##### Sit-stand workstation

Participants will receive a VariDesk Pro Plus 30 desk-mounted unit (Varidesk, TX, USA; £325 [US$405]) for the 12-week intervention period. The VariDesk unit has been selected because it is height-adjustable and noiseless, allowing both sitting and standing work with minimal disruption to others. Participants will be instructed in appropriate, safe use of the workstation by the researcher, who has received Display Screen Equipment training. A poster with images displaying ergonomically optimal desk use will be placed near the workstation, to be visible when standing or sitting. Participants will also be offered a range of tips regarding the use of the desk, including tips on physical comfort and environmental strategies to facilitate sitting reduction (e.g. leaving the desk in the raised position at the end of the workday). If it is not possible to fit the workstation during session 2, it will be fitted at a subsequent appointment as soon as possible after session 2.

A summary of key points of the session will be emailed to participants the following day. They will also be offered regular emails containing key points from the session, to serve as motivational boosters and reminders of the session, for the 12-week intervention period. Participants will be asked, in session 2, whether there are specific points that they wish to have reiterated in these emails, and how frequently they wish to receive them.

#### Qualitative data and analysis

##### Intervention session (session 2) and semi-structured interviews (sessions 3–5)

The intervention session, and semi-structured interviews undertaken at 1, 6 and 12 weeks post-baseline, will all be digitally recorded and transcribed verbatim for analysis. While participants will not be interviewed in the intervention session, their utterances will be treated as study data as they may reveal expectations of the intervention, and decisions underpinning intervention technique choices.

The three semi-structured interviews will cover the following: participants’ experiences of sitting and standing since the previous meeting; the usefulness of the sitting-reduction techniques delivered to them, including views towards the SSW; their use of the SSW and adherence to the techniques, and any suggested improvements or amendments; their perceptions of their capability, motivation and opportunity to reduce their sitting; and the conduciveness of the physical and social office environment to sitting-reduction (see Additional file 2). At 1-week post-baseline only, the interview will also cover motives for and expectations of participation and reducing sitting.

##### Analysis

Qualitative data will be analysed using inductive thematic analysis procedures, from a realist epistemological perspective [60]. Analysis will generate a set of themes that reveal which intervention components appeared acceptable and why, and which require refinement or removal from the intervention. Data will also reveal participants’ underlying beliefs, attitudes and values regarding sitting, standing and moving in the workplace, which likely act as barriers to or facilitators of workplace sitting reduction [61].

#### Quantitative data and analysis

##### Demographics

Gender, age, postcode, ethnicity, highest qualification, annual income, presence of disability and job title data will be self-reported for sample description purposes.

##### Sitting, standing and activity

Sitting, standing and sit-stand transition data will be recorded using the activPAL micro accelerometer-inclinometer (PAL Technologies Ltd., Glasgow, UK), for 7-day wear periods. The activPAL micro is small (53 × 35 × 7 mm), lightweight and provides accurate measures of sitting time and sit-to-stand transitions per hour, as validated against direct observation in free-living environments [62–64]. Sitting time data will be used to both analyse the success of the approach and to provide feedback on sitting times to participants during the intervention session.

##### Analysis

Quantitative data (accelerometry) will be extracted using specialist software designed for use with the activPAL (activPAL™ Professional v7.2.32; PAL Technologies Ltd., Glasgow, UK). Daily data will be entered into analysis only where devices have been worn for 24 h (0000 to 2359). All data will be visually inspected to identify any unusual episodes (e.g. few steps recorded, indicating the device may have malfunctioned or not have been worn), and days containing such episodes will be excluded from analyses.

Time-stamped data will be summarised in 15 s intervals and analysed in hourly intervals. Accelerometry outcomes of interest, which include daily times spent sitting, standing and stepping, frequency of sit-stand transitions and step counts, will be calculated for participants with available data on at least three weekdays and at least one weekend day. ActivPAL data distributions from a previous large observational study suggest office workers are most likely to be awake between 0700 and 2300 [12]. Daily sitting will thus be categorised as sedentary time accumulated between 0700 and 2300. Data from each 7-day observation period will be summarised for each participant, and aggregated across all participants, using descriptive statistics (means, confidence intervals). Changes in group-level aggregated accelerometry outcomes over time will be assessed using mixed-effects ANOVA, to allow for multiple measures from each participant at each of four timepoints.

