## The present study

Previous work attests to the potential efficacy of combining SSWs and motivational behaviour change strategies. Yet, few studies have adopted this approach, and only one has explored intervention acceptability among desk-based workers [30]. This paper presents the rationale for a new theory- and evidence-based intervention that combines SSWs with motivational behaviour change techniques, and a protocol for a pilot study to explore the acceptability of discrete components of a prototype of the intervention. The intervention aims to reduce sitting time, and increase standing and light activity, among office workers. The work reported here represents the early stages of a broader intervention development project.

The pilot study uses a single-group, parallel mixed-methods design, and is designed to inform subsequent refinement of intervention content, ahead of its translation into a format suitable for real-world implementation and evaluation in a randomised controlled trial. The study has two specific objectives: primarily, to inform decisions about which components to consider removing, retaining, or refining in a later iteration of the intervention, and secondarily, to inform statistical power analysis for a future trial of the intervention. The primary objective is served by qualitative interview data, which will explore the behaviour change strategies deemed by office workers to be acceptable and useful, and expectations and experiences of the intervention more broadly. We do not employ pre-specified quantifiable criteria for acceptability, but rather use qualitative analyses to explore responses relevant to acceptability from participants’ in-depth reflections on their experiences. The secondary objective is served by quantitative accelerometry data, which will document minutes spent sitting, standing and moving in the workplace before and after receiving the intervention.

The study is registered (ISRCTN29395780), and all procedures detailed in the protocol below have received approval from the King’s College London Psychiatry, Nursing and Midwifery Ethics Panel (LRS-16/17-3718).

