#### Eligibility criteria

Participants will be office- and desk-based workers aged 18 years or over who self-declare working at least 3 days per week, and whose job requires them to sit at a workstation of which they are the sole user for the majority of their typical working day. This will ensure they have sole access to the SSW for a sufficient period of time during the intervention to implement the behavioural strategies.

Workers with a physical condition which prevents standing for prolonged periods (e.g. musculoskeletal, pain, pregnancy) will be excluded. Participants must not have taken part in similar workplace standing research previously, nor ever used a SSW for two or more consecutive days. They also must not intend to leave the employer of the host site or to take an absence for longer than 10 consecutive work days for the duration of the study.

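### The secondary objective names workplace sitting, but the only sitting outcome defined covers 0700 to 2300 across a seven-day period and needs a valid weekend day

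*Protocol article*

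**What the plan says.** The section The present study gives the accelerometry one role, the secondary objective: "secondarily, to inform statistical power analysis for a future trial of the intervention". It also names the quantity. The data "will document minutes spent sitting, standing and moving in the workplace before and after receiving the intervention".

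The Analysis section under Quantitative data and analysis sets the rules:

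- **Window for sitting:** "Daily sitting will thus be categorised as sedentary time accumulated between 0700 and 2300". The reason given is that earlier activPAL data "suggest office workers are most likely to be awake between 0700 and 2300".
- **Who is included:** outcomes are "calculated for participants with available data on at least three weekdays and at least one weekend day".
- **Summary:** each seven-day period is summarised per participant and then aggregated. Change over four timepoints is tested by mixed-effects ANOVA.
- **Resolution:** the data are time-stamped, reduced to 15-second intervals and analysed by the hour.

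A 0900–1700 working day appears in two other places. Session 1 asks participants to estimate their own sitting over those hours, and the Monitoring and feedback section uses them for a graph of "the average proportion of each hour of the working day". Neither is an analysis outcome.

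The Eligibility criteria admit people who work three days a week.

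**The concern.** The objective and the analysis describe different quantities. One is confined to work. The other is a 16-hour day chosen to approximate waking time, over a period that includes days when the sit-stand desk is not in use. The article fixes this window and this validity rule itself, so this is not detail left for a later document.

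Two consequences follow. First, the change and SD passed to the future power calculation would be those of whole-day sitting, although the objective speaks of the workplace. The article's own benchmarks in the Background are also per working day (reductions of up to 30 minutes, and 2–4 hours of standing in an 8-hour day), so the planned figure cannot be set beside them directly. Second, a participant with five good workdays and no valid weekend day is lost, although weekend data say nothing about sitting at the desk. With 30 participants, avoidable losses matter.

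**Working it through.** The plan states no power-based figure to reproduce; the sample of 30 is described as pragmatic. The check is arithmetic on the article's own windows.

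**Inputs.** Analysed day: 16 h (0700–2300). Working day: 8 h (0900–1700). Days worked: five, or the eligible minimum of three. Valid days: all seven, or the minimum of three weekdays plus one weekend day. Assumptions: weekdays and weekend days are averaged together, nothing changes outside work, and the true change is an illustrative 60 minutes per workday.

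**Formulas.**

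- Work share = (days worked × 8) / (days analysed × 16)
- Apparent daily change = 60 × days worked / days analysed

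| Days analysed | Of which worked | Work share | Apparent change (min/day) |
|---|---|---|---|
| 7 | 5 | 40/112 = 35.7% | 60 × 5/7 = 42.9 |
| 7 | 3 | 24/112 = 21.4% | 60 × 3/7 = 25.7 |
| 4 (minimum) | 3 | 24/64 = 37.5% | 60 × 3/4 = 45.0 |
| 4 (minimum) | 1 | 8/64 = 12.5% | 60 × 1/4 = 15.0 |

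The last row is a three-day worker whose three valid weekdays include both non-working ones. The dilution therefore varies between participants with work pattern and with which days are valid.

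**Sample size of a future trial.** The required n is proportional to (SD/change)². Take the 5/7 case, and let v be the variance that non-work time adds, independent of the workplace change, as a fraction of the workplace variance. The whole-day variance is then 25/49 + v of the workplace variance, and

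inflation = (25/49 + v) × 49/25 = 1 + 1.96v.

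- v = 0, so the SD shrinks with the mean: inflation 1.0.
- v = 24/49 = 0.49, so the SD is equal in both windows: inflation (7/5)² = 1.96.

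The article gives no SD, so nothing in it selects a value of v.

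**After the change.** With working hours on days worked, a 60-minute change is estimated as 60. The fallback of all weekdays 0900–1700 also gives 60 for a five-day worker with those hours. For a three-day worker with all five weekdays included, it gives 60 × 3/5 = 36, so it remains a proxy.

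**The case against.** The strongest reply is that nothing is lost. Hourly, time-stamped data exist at all four timepoints, and the article already treats 0900–1700 as the working day. This stands. A reader might infer that workplace change cannot be estimated from this study; the documents do not support that. The stated analysis does not report it, but the data allow a reasonable proxy.

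The text also leaves room. The outcome list is open-ended, the 0700–2300 window is stated for sitting only, and the article does not say whether weekdays and weekend days are pooled or shown separately. The dilution figures are therefore conditional on pooling. The mismatch itself is not, since no workplace outcome is defined under either reading.

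Whole-day sitting could be the intended power input. The future trial's primary outcome is not stated, and the Study design section speaks of change in sitting without a workplace limit. That is fair, and rewording the objective would also remove the contradiction. But the objective as written says workplace.

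Three further inferences go too far:

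- **That no record of hours worked is kept at follow-up.** The article describes task logging only before the intervention, and device collection and interview afterwards. But it condenses a full protocol that is not shown, and the recorded interviews may reveal leave or absence.
- **That a participant on leave for a whole wear week would count as valid.** The criteria exclude only those intending "to take an absence for longer than 10 consecutive work days for the duration of the study", so this is possible. It needs the leave to fall between device fitting and collection, which by default are workplace visits, and is an edge case.
- **That a future trial would need nearly twice the participants.** The factor 1.96 requires an equal SD in both windows, which nothing in the article supports.

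**Conclusion.** The point holds as a mismatch between a stated objective and a stated rule. Followed as written, the plan estimates change in 0700–2300 sitting over seven-day periods, not change in workplace sitting, and can exclude participants with adequate workday data for want of a weekend day.

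If days are pooled and nothing changes outside work, 36% of the analysed hours are work time for a five-day worker with full wear. A 60-minute workday change then reads as about 43 min/day, or about 26 for a three-day worker. The effect on a later trial's size is undetermined: inflation is 1.0 if the SD shrinks in proportion to the mean and 1.96 if it does not shrink at all.

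This should be fixed, but it does not threaten the study. The objective is secondary, the pilot is exploratory with a qualitative primary objective, and most of the remedy is a redefinition applied to data already being collected.

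**What to change.** In the quantitative Analysis section, add as the outcome for the secondary objective the minutes spent sitting, standing and stepping during working hours on days worked. Use weekdays 0900–1700 as the default where actual hours are unknown; this can be derived at all four timepoints. Base validity for this outcome on workdays, with a threshold that a three-day worker can meet and no weekend-day requirement. Keep 0700–2300 sitting as a separate whole-day outcome, and say whether its weekdays and weekend days are pooled.

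If the full protocol does not already provide for it, note the days and hours worked when each device is collected. This reduces misclassification of part-time days, leave and shifted hours.

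The cost is revised wording, a second summary of data already extracted by the hour, and a brief note at each device collection. The downside is small: hours would be self-reported, and unavailable for weeks already collected, which would rely on the 0900–1700 default. The trial status section reports that recruitment and data collection are under way, so the note is worth starting soon.

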## Discussion

Evidence increasingly suggests that sitting time is a risk factor for morbidity and early death [2–4]. We are developing a novel sedentary behaviour reduction intervention, based on a theory- and evidence-based analysis of why office workers sit and how best to reduce sitting. The intervention combines two approaches—provision of SSWs, and motivational support—that have separately shown promise for reducing sitting time [15, 27]. We will pilot a prototype of the intervention among a sample of 30 office workers at a UK university. Novel elements of our intervention are that the motivational support intervention component is tailored to theory-derived determinants of sitting reduction, and that, in engaging participants in selecting from a menu of intervention techniques, our participants will co-design their intervention and its implementation. This participatory approach may enhance intervention effectiveness [34, 35]. Our pilot study will be the first, to our knowledge, to explore direct feedback on the acceptability of discrete tailored sitting-reduction intervention components. Acceptability is an important determinant of intervention success [37], but has been largely overlooked in the development and testing of sitting-reduction interventions to date. Results will inform the refinement of intervention content, as a subsequent stage in an overarching intervention development project.

Applying theory to intervention design allows scientific knowledge about behaviour change to be used in specifying the techniques most likely to change behaviour, and the mechanisms through which such change might be achieved [65]. Yet, few workplace sitting-reduction interventions evaluated to date have been explicitly theory-based [15]. There are multiple ways in which theory can inform interventions [66]. Drawing on the COM-B model [38], our intervention delivers change techniques tailored to participants’ self-reported capability, opportunity and motivation to reduce sitting. There are limitations to this approach; participants may not be aware of the true barriers to their sitting [67], and so the techniques they choose to receive may lack efficacy for reducing their sitting time. Nonetheless, it seems prudent to identify the intervention content with which office workers are most (or least) likely to engage. Interventions that are not acceptable to office workers are unlikely to be implementable.

We will adopt an exploratory qualitative approach to investigate intervention acceptability, probing participants’ reflections to identify elements they did or did not find useful, interesting, engaging, or otherwise pertinent. We did not consult directly with office workers to generate intervention content at the outset of the intervention development process. Studies reporting workers’ ideas for sitting reduction have tended to yield similar suggestions (e.g. SSWs, computer prompts, standing meetings, removing chairs, education [16, 21, 22, 39]). We have incorporated many of these suggestions into our intervention as advice for identifying and seizing opportunities to sit less. We will instead explore the acceptability of core components of our intervention among workers who have attempted to engage with it. One limitation is that our qualitative methods will not quantify acceptability, precluding evaluation against a predetermined threshold. Conversely, however, qualitative methods allow for in-depth coverage of the reasons underlying acceptability [61]. This will help us to identify whether and how discrete components require modification in the next iteration of the intervention. Furthermore, views expressed by our intervention recipients towards a sitting-reduction intervention have the potential to generate new knowledge of office workers’ underlying beliefs, attitudes and values towards workplace sitting and activity, which may not be revealed by direct questioning [61].

One potential limitation of our study is that acceptability is explored among intervention recipients only. The feasibility of workplace sitting-reduction interventions depends on acceptability not only among office workers but also managers [30, 33]. Senior management at the study site—a UK university—may have a more positive and open attitude towards testing novel, evidence-based sitting-reduction interventions than other employers. Research has documented doubts among employers about the benefits of sitting reduction [22]. Furthermore, the intervention prototype we will test is resource-intensive, requiring one-to-one behavioural counselling from a trained psychologist. This is unlikely to be scalable; office managers may not be willing to fund provision of such support or may not want workers to attend such sessions during working hours. Indeed, office workers may not be willing to attend lengthy one-to-one appointments if they are seen to reduce time available for pressing work tasks [22]. However, the present study represents a step towards developing a scalable intervention acceptable to employers and workers alike. We will use the findings from the present study to inform a refinement of the intervention that can be delivered in a less resource-intensive way. Tailored self-administered computer-based interventions, for example, can effectively mimic face-to-face behavioural counselling [68]. While we note that a recent computer-based sitting-reduction intervention was found to have no impact on objectively measured sitting time [24], this may have been due to the selection of content included in the intervention, rather than the delivery format. At a later stage in the development process, we intend to translate content of the intervention prototype that is deemed acceptable in the present study into a self-administered format. As a precursor to further intervention development work, an additional limitation of the present study is that participants’ views will necessarily be based on experiences of one-to-one delivery of intervention components. While we will attempt to identify insights that would likely apply across delivery methods, we may need to conduct further work to determine whether amending the delivery format affects the acceptability of intervention components.

Another limitation of our study is that it targets sitting reduction primarily by addressing the needs of individual workers. Such an individual-level conceptualisation of sitting reduction could be argued to neglect broader determinants of workplace sitting behaviour. Ecological models portray sedentary behaviour as the product of a complex interplay of individual, organisational and environmental factors [69]. Achieving sustainable reductions in workplace sedentary behaviour may require not only changes in workers’ motivation and capability, and the provision of more opportunities, but also commitment from senior management to the creation of organisational and cultural norms supporting standing and light movement [33]. The aims of the present study are, however, consistent with a broader ecological approach. Managers are unlikely to want to commit resources to support intervention strategies that are shown to lack acceptability among office workers [22]. Our study will help to identify discrete sitting-reduction intervention components with which office workers are most willing to engage.

